## Abstract

**Introduction:**

Arteriovenous fistulas (AVFs) are considered the best and safest modality for providing haemodialysis in patients with end-stage renal disease. Only 20% of UK centres achieve the recommended 80% target for achieving dialysis of the prevalent dialysis population via permanent access (as opposed to a central venous catheter). This is partly due to the relatively poor maturation rate of newly created fistulas, with as many as 50% of fistulas failing to mature.

The Surveillance Of arterioveNous fistulAe using ultRasound study will examine whether a protocolised programme of Doppler ultrasound (US) surveillance can identify, early after creation, potentially correctable problems in those AVFs that subsequently fail to mature.

**Methods and analysis:**

This is a multicentre observational study that will assess newly created AVFs by Doppler US performed at 2, 4, 6 and 10 weeks after creation. The primary outcome measure will be primary fistula patency at week 10. Secondary outcome measures include: successful use of the fistula; clinical suitability for dialysis; creation of new fistula or radiological salvage; fistula thrombosis; secondary fistula patency rate and patient acceptability.

**Ethics and dissemination:**

The study has been approved by the Cambridgeshire and Hertfordshire Research Ethics Committee and by the Health Research Authority (REC 18/EE/0234). The results generated from this work will be published as open access, within 3 years of trial commencement. We will also present our findings at key national/international renal meetings, as well as support volunteers at renal patient groups to disseminate the trial outcome.

**Trial registration number:**

ISRCTN36033877

Strengths and limitations of this studyIt is a prospective observational multicentre study that examines whether a programme of Doppler ultrasound (US) surveillance can identify those newly created arteriovenous fistulas (AVFs) that are unlikely to mature.The demonstration that US surveillance can successfully identify newly created AVFs that are unlikely to mature will prompt a second-phase prospective randomised study, in which ‘at-risks’ fistulas are randomised to continued observation (control arm) or attempted surgical/radiological salvage.The second-phase study will use the same centres and trial expertise as assembled for the initial observational study and would represent the largest vascular access study yet performed, with ~1200 participants.The main limitation of this study is that the primary endpoint uses a surrogate marker of fistula patency (based on US flow characteristics) rather than an independent and functionally relevant endpoint (successful use of the fistula for dialysis).

## Introduction

The kidneys provide a number of key functions, including the excretion of excess fluid and harmful toxins. In patients with end-stage renal disease (ESRD), the excessive build-up of toxins and fluid would be fatal if left untreated. Consequently, patients with ESRD require renal replacement therapy in the form of either kidney transplantation or dialysis. About 70% of patients requiring dialysis opt for haemodialysis (equating to about 20 000 patients a year in the UK).^1^

Arteriovenous fistulas (AVFs) are considered the best modality for providing haemodialysis in patients with ESRD, because haemodialysis via a central venous catheter (CVC) is associated with increased incidence of bloodstream infection, hospitalisation and cost.^2–8^ Patient mortality for patients dialysing via a CVC is about 40% higher than for patients dialysing via an AVF.^9^

Only 20% of UK dialysis centres currently achieve the 80% Renal Association target for dialysis of their prevalent population via definitive access (rather than a CVC).^1 10^ The reasons why such a small proportion achieve dialysis via an AVF are multifactorial, but the relatively poor maturation rate, with as many as 50% of fistulas failing to mature, undoubtedly contributes. Although this may reflect suboptimal arterial inflow that is difficult to rectify, stenosis due to venous intimal hyperplasia also contributes and is potentially correctable by either radiological or surgical intervention. If so, the improved assisted primary fistula patency is likely to increase AVF usage substantially, as well as saving money by avoiding the need to create a further AVF or to dialyse via a CVC. Increased AVF usage may result in improved patient survival by avoiding CVC-related complications and by preserving precious venous ‘capital’ for future fistula formation.

The literature relating to ultrasound (US) surveillance of AVFs is conflicting. This may reflect variations in the type of surveillance adopted, the type of fistula under surveillance and the precise US scanning method. US can reliably identify fistulas that have successfully matured,^11 12^ and although the precise ultrasonic characteristics that constitute a mature fistula continue to be debated,^13^ adoption of a surrogate US definition of maturity avoids exclusion of predialysis patients from vascular access trials.

Few studies have attempted to use US to characterise early maturation, immediately after fistula creation, but those that do suggest that successful fistula maturation is associated with rapid increase in fistula blood flow, even by the first day after formation.^14 15^ Fistula vein diameter may also increase rapidly.^15^ Thus, assessment at these earlier time points may be predictive of later patency. In a study of 153 patients, Itoga *et al* performed early duplex US on newly formed fistulas (4–8 weeks after creation).^16^ A flow limiting stenosis was detected in 40% of patients, of whom 81% underwent subsequent radiological intervention. Assisted primary patency of the fistulas in this group (compared with the cohort without detectable US abnormality) was 83% versus 96% at 6 months and 64% versus 89% at 1 year. There was no control cohort (patients who did not undergo routine surveillance), but the assisted patency reported for the entire study population would appear to be better than generally reported following fistula creation. One randomised study has evaluated routine early US surveillance (2, 4 and 8 weeks after fistula creation, 150 patients) and reported a 13.6% fistula failure/non-maturation rate in the surveillance group, compared with 25.4% in the control group in whom US was performed on the basis of a perceived clinical indication.^17^ This difference did not reach statistical significance, but notably, the study was powered for a 20% difference in maturation. Our proposed study is powered for a 10% difference, with a corresponding increase in numbers of enrolled patients.

### Rationale for study

Only 20% of UK dialysis centres manage to meet the Renal Association guidelines to dialyse their prevalent population via an AVF. Numerous factors contribute to this, but the high early failure rate, with as many as 50% of nascent fistulas failing to mature, is undoubtedly a major factor.

At present, the paucity of evidence suggesting surveillance increases rates of dialysis via the fistula alongside the significant cost and required resources leads to significant heterogeneity in practice across the UK and internationally. This study aims to fill this gap in knowledge by determining whether US surveillance of newly formed AVFs can be used to identify failing fistulas.

We aim to demonstrate whether a structured programme of Doppler ultrasound (US) surveillance will accurately predict structural abnormalities (such as venous intimal hyperplasia) that lead to the failure of a newly created fistula to adequately develop and provide effective access for dialysis. We hypothesise that these detected structural abnormalities would be amenable to correction by interventional radiology or surgery, leading to improved assisted fistula patency. This would likely increase AVF usage substantially, as well as potentially save money by avoiding the need to create a further AVF or to dialyse via a CVC. Increased AVF usage may result in improved patient survival by avoiding CVC-related complications and by preserving precious venous ‘capital’ for future fistula formation.

#### When after fistula creation should US surveillance be performed?

Although 1 year unassisted fistula patency (primary) is approximately 55%, about 60% of these failures will occur within the first 3 months after creation,^18 19^ and it is likely that failures in the first year relate to individuals whose fistula had never developed optimally.^20 21^ This study therefore assesses US surveillance of the fistula during its maturation phase, immediately after creation.

We feel that for a trial to demonstrate that US surveillance improves patency rates for newly created fistulas, two conditions must be met:US can effectively distinguish those newly formed fistulas that are unlikely to mature.Salvage interventions performed on those ‘at-risk’ fistulas are effective.

### Study design

These conditions will be addressed in two phases:

Phase I: A prospective observational cohort study to first determine whether US surveillance can reliably predict fistula failure.

Phase II: A prospective randomised trial that examines 1-year fistula patency and compares US-directed fistula salvage against standard clinical assessment (no US surveillance).

This study protocol covers only phase I of the study. We will only move on to phase II if US is found to be effective at identifying ‘at-risk’ AVFs: this will be covered by a separate protocol. The outputs of phases I and II will form the primary inputs into a decision model predicting the incremental cost effectiveness of US surveillance versus standard clinical assessment.

Phase I will recruit patients who are either predialysis or already established on haemodialysis via a central venous catheter (see figure 1). Consenting patients will undergo serial US scanning at weeks 2, 4, 6 and 10 after fistula formation in addition to standard care (such as regular clinical assessment) as per local centre policy. The US findings will be blinded, that is, will not be relayed to the participant or to the participant’s clinical team.

**Figure 1 F1:**
[figure not shown]
SONAR study flow chart flow chart of patient journey from screening and enrolment through to final study scan and clinical assessment within the SONAR trial. AVF, arteriovenous fistula; SONAR, Surveillance Of arterioveNous fistulAe using ultRasound.

### Potential benefits and risks of study

The only direct benefit to the participating patient is the detection of fistula thrombosis at an earlier juncture than would normally occur with routine clinic follow-up. We anticipate, however, that the incentive to participate in a trial that clarifies the role of US surveillance of newly formed AVFs will enable recruitment rates to be met.

Doppler US is a low risk form of imaging, as it does not use ionising radiation, and as such this observational study poses very low risk to participants. Acoustic power output and duration of exposure to US should not exceed those of a typical diagnostic examination, with exposure kept as low as reasonably achievable.^22^ While no patient injury has been recorded from non-contrast-enhanced US at diagnostic levels, bioeffects including significant heating and cavitation have been demonstrated at higher intensities.

## Methods and analysis

### Study hypothesis

Doppler US surveillance can reliably predict failing nascent AVFs by identifying potentially correctable anatomical defects.

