### Sample size

We have estimated that 20% of fistulas fail early and that early US has a positive predictive value (PPV; number of true positives/number of predicted positives) of 72% for predicting non-maturation. To estimate this with ±10% precision (ie, the 95% CI is from 62% to 82%), 78 predicted failures are required. We estimate that US predicts failure in 25% of fistulas meaning 312 fistulas are required in the study. Allowing for 10% dropout, 347 fistulas will be recruited. To predict primary fistula patency for the phase II trial (not part of this protocol), we anticipate that two models will be required and therefore we will have two PPVs—one for wrist fistulas and one for elbow fistulas. Assuming a ratio of 50:50 for wrist to elbow fistulas, the precision CI will be from 55.3% to 85.2%.

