#### Analysis of primary and secondary outcomes

The primary fistula patency rate at week 10 will be calculated alongside an exact 95% CI based on all participants enrolled. It will also be calculated based on participants whose fistulas did not fail early. Patency will be assessed using the results from each US scan up to week 10.

The secondary outcomes will be presented using descriptive summary statistics.

Mixed multivariable logistic regression will be used to model primary fistula patency by 10 weeks, which will then be used as a risk-score calculator in the phase II trial. Two models will be built, one for wrist fistulas and one for elbow fistulas. Measurements taken from the first scan performed at week 2 will be considered as parameters in the model initially, and further parameters from either the second scan or the third scan will then be considered. The choice of second or third scan will be based on the best fitting parameters, as assessed by significance level. A random effect for the participant will be included in the models to account for multiple scan data per participant. The aim will be to build parsimonious models, which contain the minimum number of measurements required to effectively predict primary fistula patency. A receiver operating characteristic curve analysis of the developed risk scores will be used to assist decisions regarding an appropriate cut-off for an indicator for when intervention is required for both wrist and elbow fistulas. The PPV will be calculated alongside an exact 95% CI for the chosen risk score cut-off.

It is anticipated that some participants will not attend all scans, and therefore, some scan data will be missing. Levels of missing data will be summarised for each of the scan time points and will be considered when choosing which scan results to use in the final model. Any missing primary and secondary outcome data will not be imputed. Missing data for parameters in the modelling of primary fistula patency will be imputed using multiple imputation if the level of missing data is greater than 10%.

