## Discussion

Surveillance Of arterioveNous fistulAe using ultRasound (SONAR) will be one of the largest observational vascular access studies yet performed. If Doppler US accurately identifies anatomically correctable lesions that are preventing maturation (‘salvageable fistula’), this will be used to power and justify a second phase interventional study that addresses whether timely surgical and/or radiological intervention improves fistula patency rates. Conversely, if the SONAR study does not identify a role for routine Doppler US surveillance of newly formed arteriovenous fistulas, this would have immediate relevance for studies in other countries that are similarly using Doppler US to assess fistula maturation.^15 21 23^

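### The hypothesis turns on correctable defects, but no described analysis links predicted failures to one, and PPV is the only accuracy estimate sized and promised with an interval

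*Protocol article*

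**What the plan says.** Three sections of the protocol article state the purpose in terms of defects.

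- Study hypothesis: "Doppler US surveillance can reliably predict failing nascent AVFs by identifying potentially correctable anatomical defects".
- Rationale for study: the aim is to predict structural abnormalities, with venous intimal hyperplasia as the example, that stop a fistula developing.
- Discussion: the interventional study is to be powered and justified on a condition that begins "If Doppler US accurately identifies anatomically correctable lesions that are preventing maturation".

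The Introduction separates two causes of failure: poor arterial inflow, described as hard to put right, and venous stenosis, described as potentially treatable.

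Analysis of primary and secondary outcomes describes one mixed logistic model for wrist and one for elbow fistulas, each for patency by 10 weeks. Primary outcome measure defines that endpoint by vein diameter and blood flow. Predictors come from the week-2 scan and then from the second or third scan, with significance guiding that choice and parsimony as the goal. A ROC analysis helps to set the cut-off. Then: "The PPV will be calculated alongside an exact 95% CI for the chosen risk score cut-off".

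Sample size gives the planning inputs: "We have estimated that 20% of fistulas fail early", a PPV "of 72% for predicting non-maturation", and 25% of fistulas predicted to fail. Study design makes phase II depend on US proving effective at picking out at-risk fistulas and does not define that further.

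**The concern.** The question asked and the analysis described do not meet. The hypothesis has two parts: US predicts failure, and it does so by finding something that could be corrected. The model and its PPV address the first part only.

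Diameter and flow define the endpoint and are also measured at every scan. A parsimonious score could therefore consist of early diameter and flow, perform well, and contain no stenosis term. Such a score might mainly flag fistulas with poor inflow, which the Introduction regards as hard to rectify. Phase I would then appear to support a salvage trial without having shown that the flagged fistulas have anything to salvage.

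The second strand is the choice of PPV as the one accuracy estimate that is sized and given an interval. PPV describes the flagged fistulas. It does not say what share of all failures is flagged, and a surveillance programme needs to know that too.

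**Working it through.** **1. The plan's own figures reproduce.** Inputs from Sample size: PPV p = 0.72, half-width d = 0.10, flagged share q = 0.25, dropout 10%.

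- Predicted failures: 1.96² × 0.72 × 0.28 / 0.10² = 77.4, rounded up to 78.
- Fistulas: 78 / 0.25 = 312. Recruited: 312 / 0.90 = 346.7, rounded up to 347.
- Per site, with 39 predicted failures and 0.72 × 39 = 28.08 true positives, the exact interval is 55.3% to 85.2%, as stated.

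The size calculation is sound for PPV. No other accuracy measure enters it.

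**2. What the inputs imply.** With failure rate π:

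- Sensitivity = pq/π = 0.18/π
- Specificity = 1 − q(1 − p)/(1 − π) = 1 − 0.07/(1 − π)
- NPV = 1 − (π − 0.18)/0.75

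At π = 0.20, sensitivity is 0.18/0.20 = 90%, specificity is 1 − 0.07/0.80 = 91% and NPV is 1 − 0.02/0.75 = 97%. The protocol does not state these figures.

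**3. How far PPV leaves sensitivity open.** Other rates can be read from the document. One-year failure of 45%, with 60% of it in the first 3 months ("Although 1 year unassisted fistula patency (primary) is approximately 55%, about 60% of these failures will occur within the first 3 months after creation"), gives 0.45 × 0.60 = 27%. The Introduction also says "with as many as 50% of fistulas failing to mature". Holding q and p fixed, as an assumption:

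| Failure rate | Sensitivity | Specificity | NPV | Failures missed among 312 |
|---|---|---|---|---|
| 20% | 90% | 91% | 97% | 6 of 62 |
| 27% | 67% | 90% | 88% | 28 of 84 |
| 50% | 36% | 86% | 57% | 100 of 156 |

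Sensitivity falls below 50% once π exceeds 0.18/0.50 = 36%. The PPV is 72% in every row.

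**4. The alternative assumption.** Hold sensitivity at 90% and specificity at 91.25% instead. At π = 0.50 the flagged share becomes 0.50 × 0.90 + 0.50 × 0.0875 = 49%, and PPV becomes 0.45/0.494 = 91%. The low sensitivities in step 3 therefore come from freezing the flagged share and PPV. They show what PPV permits and are not a forecast.

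**5. Hypothesis against analysis.** Flow-limiting stenosis is recorded (Doppler US surveillance), so it may be a candidate predictor. Nothing requires the model to keep it, and no described tabulation asks how many predicted failures show it. Analysis plan also keeps in the analysis population fistulas that failed within 2 weeks of surgery. If these were counted as predicted failures, they would raise PPV without any prediction having been made.

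**The case against.** The strongest reply is that the protocol divides the work. Study design gives phase I the task of showing that US predicts failure and leaves salvage to phase II, so prediction of failure from any cause meets phase I's stated purpose. Sensitivity, specificity and cross-tabulations at a cut-off are also commonly left to an analysis plan, which is not shown here.

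Part of this stands. Whether salvage works is a phase II question, and the missing tabulations alone would be no finding. But whether a flagged fistula has a visible, potentially correctable lesion is part of the hypothesis that phase I itself states. The mismatch is between two things this document fixes.

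Several stronger readings are tempting, and the documents do not support them:

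- *PPV is the only accuracy measure planned.* A ROC analysis is planned, so sensitivity and specificity bear on the cut-off. What is lacking is a promised estimate of either.
- *72% is a target, and phase II is decided on PPV.* The 72% is a planning value for precision, and Study design does not tie the decision to PPV.
- *Most failures will be missed.* At the plan's own inputs 90% are caught. The 36% needs 50% failure with the flagged share frozen at 25%, although that share follows from the cut-off.
- *The hypothesis is never tested.* Stenosis is recorded and may enter the model. The fair statement is that no described analysis tests that part.
- *20%, 27% and 50% contradict one another.* They differ in definition and time horizon: early failure, a 3-month figure derived here from one-year patency, and an upper figure for non-maturation with no time point.

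**Conclusion.** The concern holds in a limited form. The hypothesis, the aim and the case for phase II concern correctable defects, while the described analysis models week-10 patency whatever the cause of failure and need not retain stenosis. That gap needs no arithmetic or outside figure to show.

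The accuracy strand is secondary. PPV is the only estimate sized and promised with an interval, and the same 72% is compatible with sensitivity of 90%, 67% or 36% at failure rates of 20%, 27% or 50%. Those last two values rest on holding the flagged share and PPV fixed. It is also unclear whether the 20% that fail early is the rate of the week-10 endpoint, since the PPV beside it is worded for non-maturation. This is an ambiguity to resolve and does not show that the 20% is wrong.

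**What to change.** In Analysis of primary and secondary outcomes:

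- Among predicted failures not already thrombosed at the predicting scan, report the proportion with a flow-limiting stenosis, with an exact 95% CI, as a proxy for a correctable defect. If all 78 predicted failures qualified, the half-width would be at most about 1.96 × √(0.25/78) = 11 points by the normal approximation. It would be wider with fewer, or by site.
- At the chosen cut-off, report sensitivity, specificity and NPV with CIs beside PPV. Give the observed failure rate as the benchmark, since an uninformative score has a PPV equal to it.
- State that these results will be weighed together with PPV in judging whether US is effective enough for phase II.

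In Sample size, say whether the 20% is the rate of week-10 non-patency to which the 72% applies, and state the implied sensitivity of 90% and specificity of 91%.

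The cost is a few extra tabulations of data already on the proforma, and some wording. No scan, visit or participant is added. The limitation is that stenosis on US is only a proxy for a lesion that could be corrected, and the report should say so.
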